### **Potential covariates**

Trail Making Parts A&B – The Trail Making Test is a widely used test of executive cognitive function(72) that involves multiple cognitive domains and is administered in two parts. Completion of the Trail Making Test A (TMT-A) involves complex visual scanning, motor speed, and agility as participants draw lines to connect consecutively numbered circles as quickly as possible. Completion of Trail Making Test B (TMT-B) requires the additional processes of cognitive flexibility and set shifting as participants connect circles in an alternating sequence of numbers and letters, linking them in ascending order as fast as possible. Time to complete and number of errors for each portion will be recorded. Lower scores (faster times) indicate better performance.

Geriatric Depression Scale (GDS)(73) – The Geriatric Depression Scale has been used extensively in community-dwelling healthy and medically ill older adults to screen for depression. The short form GDS consists of 15 yes or no questions. Scores of 0-4 are considered normal, scores of 5-8 indicate mild depression, scores of 9-11 indicate moderate depression and scores of 12-15 indicate severe depression.

Pittsburgh Sleep Quality Index(74) – The Pittsburgh Sleep Quality Index is a self-rated questionnaire which assess sleep quality and disturbances over a 1-month time period.

Nineteen individual items generate seven “component” scores: subjective sleep quality, sleep latency, sleep duration, habitual sleep efficiency, sleep disturbances, use of sleeping medication and daytime dysfunction. The sum of the scores for the seven components yields a global score.

Life Space Mobility(75) – The University of Alabama at Birmingham (UAB) Study of Aging Life-Space Assessment (LSA), measures a person’s usual pattern of mobility in the previous month. Life-space can be visualized as a pattern of areas defined by distance extending from the location where a person sleeps. The LSA allows for a range of mobility assessment from limited to the room where the person sleeps with assistance from another person to independently traveling out of town. The LSA documents mobility based on how far and how often a person travels and the amount of assistance that is needed. Scores range from 0 (totally bed-bound) to 120 (travelled out of town every day without assistance). Higher scores indicate a greater mobility.

Gait Efficacy Scale. In order to determine if changes in walking difficulty are associated with changes in confidence in walking, confidence will be assessed using the Gait Efficacy Scale.(76) The items include a range of gait activities such as walking over different surfaces, up and down curbs, and negotiating stairs. Each item has a 10 point Likert scale scoring option, with the total score for the 10 items, ranging from 0-100. A higher score represents greater confidence.

### 6.2.3 Follow-up Visits

Follow-up visits will occur at 12 (conclusion of the intervention), 24 and 36 weeks post randomization. Windows for follow-up testing are as follows: 12±2weeks, 24 -2/+4 weeks, and 36 -2/+4 weeks. Measurements will include the following:

#### 12, 24, and 36 weeks:

- Gait Speed
- Lower extremity strength and power
- Six minute walk test
- Chair sit and reach test
- Smoothness of walking
- Gait Efficiency
- Figure of 8 walk test
- Gait Efficacy Scale
  
- LLFDI
- Physical Activity – Actigraph
- Trail Making Parts A&B
- Geriatric Depression Scale
- Pittsburgh Sleep Quality Index
- Life Space Assessment

## **7 SAFETY ASSESSMENTS**

### **7.1 Participant Safety Parameters: Methods and Timing**

#### **7.1.1 Screening**

Potential participants will be excluded during the screening phases if they have persistent pain (lower extremity or back) that would interfere with participation or if they are medically unstable or have medical conditions which may impact their safety (see exclusion criteria). Individuals with resting systolic blood pressure  $\geq 200$  mm Hg or diastolic blood pressure  $\geq 100$  mm Hg or resting heart rate  $> 100$  or  $< 40$  beats per minute will also be excluded. All participants must also have physician clearance to participate in a moderate intensity exercise program prior to the start of the exercise intervention.

#### **7.1.2 Safety Considerations for Assessments and Interventions**

##### **Expected Adverse Experiences**

1. Major risks such as a cardiac event or a fall are expected to be rare – expected to occur in less than 1% of people (less than 1 out of 100 people). Gardner et al, 2000,(77) reviewed controlled clinical trials of exercise interventions for older adults at-risk for falling. No cardiac events or falls were reported in the 12 clinical trials reviewed. The at-risk older adults in the studies reviewed have slightly poorer physical performance than the older persons we expect to recruit for our study. In our recent MOBILE study, a 1 year cohort study of 120 older adults participating in 3 clinic visits over a 1 year period there were no cardiac events or falls reported. In all conditions of testing in which the participant is standing and/or walking (eg conditions with a potential risk for falling), the participant will be directly supervised by the physical therapist. The physical therapist is present for all testing sessions. We expect this level of supervision reduces the risk of falling to an even greater degree.
2. Less severe risks of participation such as muscle soreness, fatigue, or minor sprains or strains with each assessment, are expected to be infrequent – expected to occur in 1-10% of people (1-10 out of 100 people). Gardner et al, 2000,(77) reviewed controlled clinical trials of exercise interventions for older adults at-risk for falling, finding reports of such side effects of the intervention reported in only 4 of the 12 studies reviewed. The side effects were not a reason for dropout from the study and were described as soreness or musculoskeletal symptoms, but no injuries.
3. There is a rare risk that confidentiality could be breached. All of the research records will be kept in a locked file cabinet and/or password protected files. All of the investigators and staff that assist with the management of the files are trained in the privacy and confidentiality regulations that govern research.

##### **Minimizing Risk during Assessments and Interventions.**

All assessments approved in this study are considered to be a part of everyday clinical practice. We have minimized risks we believe by applying usual safeguards for the physical therapy assessment of gait. Assessment side effects, such as muscle soreness, fatigue, or minor sprains or strains with each assessment, will be recorded by the physical therapist and monitored by [name], the Principal Investigators in consultation with the physician investigator, [name]. Based upon the existing literature and our own clinical experience, we anticipate the frequency of these side effects to be extremely low.(77)

We will maximize the safety of our subjects with the following procedures.

1. Individuals with absolute contraindications to testing will be excluded based on the inclusion/exclusion criteria.
2. Testing will be carefully monitored by a licensed physical therapist and will be adjusted according to the American College of Sports Medicine Guidelines for Exercise Testing and Prescription.(35)
3. In all conditions of testing in which the participant is standing and/or walking (eg conditions with a potential risk for falling), the participant will be directly supervised by the physical therapist.
4. Subjects will be required to get medical clearance from their primary care physician prior to initiating the exercise intervention.

### **Confidentiality.**

Participant's confidentiality will be protected in the data collection process. All personnel involved with the research have read and signed a Confidentiality statement, and approval is being obtained from the University of Pittsburgh Biomedical Institutional Review Board. Consent forms and data collection forms that identify the participant by name will be stored in a locked cabinet. All computers are password protected. If the data are used in scholarly presentations or journal articles, the investigators will protect the anonymity of individual participants and will report only aggregate data (eg group means) where appropriate. The Principal Investigator will review data confidentiality processes monthly or as indicated with the project staff (Study coordinator and Physical Therapists). The Investigators are all certified in Research Practice Fundamentals, Human Subjects Research Module.

### **Management of Adverse Experiences**

All assessments and exercise interventions will be delivered in the Physical Therapy Clinical and Translational Research Center (PT-CTRC). The emergency procedures are posted within the PT-CTRC (see attached) along with an AED. Emergency procedures are reviewed with the staff every 6 months. All PT-CTRC staff are certified in the American Heart Association BLS for Healthcare Providers (CPR and AED) program. Blood pressure and heart rate will be routinely monitored before and after the exercise interventions. Any symptoms that occur during activities performed by the participant as instructed by the study intervention protocol will be monitored and acted upon. Cardiac

symptoms will include the following: chest pain, shortness of breath, dizziness, syncope, lightheadedness, arm pain or numbness, acute onset fatigue/exhaustion, palpitation or fluttering in the chest, sweating and feeling of heart racing, acute onset severe headache, weakness or numbness in on one side, part or whole body, speech difficulties and fall to a lower level or floor. Cardiac signs will include the following: extremes of blood pressure or heart rate abnormality, wheezing, leg cramps or claudication, confusion or an acute change in participants' mental status, unresponsiveness or sluggish responses, fever, change in color of skin. Some of these activities may occur on the physical premises of the study site. If cardiac symptoms or signs arise during the exercise component of the intervention or in the physical premises, the staff will immediately terminate the exercise ensuring that the participant is seated or lying supine. Research staff will closely monitor the participant and if a medical emergency should occur, staff will immediately follow BLS procedures and call 911. They will describe the incident to the 911 operator and provide their location ([name]). Once the emergency situation is under control, the staff will contact the study coordinator and PI to notify them of the situation. If the symptoms are not serious enough to warrant CPR or to call 911 they will follow the procedures outlined in the manual of operations.

#### Participant Education about Potential Risks

Potential risks associated with study-related activities and interventions will be explained to each participant by trained study personnel during the informed consent process. Each participant will be instructed to report the occurrence of an AE to appropriate study staff at scheduled data collection times, to PTs administering the intervention, or spontaneously at any other time. Participants also will be encouraged to report concerns about the safety of participating in the study to any research staff.

## **8. Adverse Events and Serious Adverse Events**

### **8.1 Overview**

Expected adverse events (AEs) will be captured through interviews at 12, 24 and 36 weeks, based on the Health Status Update questionnaire. Reportable events are those events that have potential implications for participant safety and require individual reporting. Reportable AEs are defined as), AEs that have potential implications for participant safety, unexpected AEs, and injury that occurs while a participant is under the supervision of study related personnel. These RAEs will require individual event reporting as described in section 8.4. The timely and complete account of RAEs will be a critical requirement for the protection of human subjects in this trial.

The DSMB will review and approve study-defined expected AEs and will be involved in the regular monitoring of the RAE reporting system. Reporting of expected AEs to the DSMB, the NIA, and the IRB will be through the database. RAEs will be monitored and tracked separately and reviewed by the DSMB and the NIA as outlined in section 8.4.

### **8.2 Classifying Adverse Events**

An AE is any unfavorable or unintended medical occurrence in a human study participant that has taken place during the course of a research project, including any

abnormal sign, symptom, or disease, whether or not related to participation in the research.

For the purposes of this study, any event that meets the criteria for an SAE, is unexpected, or results in injury to the participant while he/she is under the supervision of study related personnel will be classified as an RAE. Adequate review, assessment, and monitoring of RAEs require they be classified as to severity, expectedness, and potential relatedness to the study intervention.

#### 8.2.1 Severity

The following guidelines will be used to determine level of severity:

**Mild:** Awareness of signs and symptoms, but easily tolerated and causing no loss of time from normal activities. No specific medical attention is required.

**Moderate:** Discomfort enough to cause a low level of inconvenience or concern to the participant and may interfere with daily activities. Symptoms may require minimal, local or noninvasive medical intervention.

**Severe:** Events interrupt the participant's normal daily activities and are usually incapacitating. Significant symptoms may require hospitalization or invasive medical intervention.

**Life-threatening/Disabling:** Events that may involve acute, life-threatening metabolic or cardiovascular complications (such as circulatory failure, hemorrhage, sepsis) or life – threatening physiological consequences. Intensive care or emergent invasive procedure is required.

**Death:** Causing death.

Severity is not synonymous with seriousness. A severe headache is not necessarily an RAE. However, mild chest pain may results in a day's hospitalization and thus would be classified as a RAE.

#### 8.2.2 Expectedness

AEs will be assigned as to whether they were expected or unexpected based on current knowledge. Categories are defined as follows:

**Expected:** An AE that is anticipated on the basis of prior experience with the intervention under investigation; an event that can be attributed to the underlying condition of the participant being studied; or an event that can be attributed to the patient population being studied (see section--- Expected AEs). Expected AEs are captured in a standardized way by study personnel.

**Unexpected:** An AE that was not anticipated on the basis of prior experience with the underlying intervention under investigation; an event that can be attributed to the

underlying condition of the participant being studied; or to the patient population being studied or an expected event whose frequency or severity exceeds what is anticipated. Unexpected events are reportable.

### **8.2.3 Relatedness**

The PI in consultation with the Co-Investigators and an independent safety monitor will determine the degree to which RAEs are related to study procedures using the criteria below.

Definitely related: The adverse event is clearly related to the investigational procedure – i.e., an event that follows a reasonable temporal sequence from administration of the study intervention, follows a known or expected pattern of response to the study intervention, that is confirmed by improvement on stopping and reappearance of the event on repeated exposure, and that could not be reasonably explained by the known characteristics of the participant's clinical state.

Possibly related: An adverse event that follows a reasonable temporal sequence from administration of the study intervention of that follows a known or expected pattern of response to the study intervention, but that could readily have been produced by a number of other factors.

Unrelated: The adverse event is clearly not related to the investigational procedure (i.e. another cause of the event is most plausible; and/or a clinically plausible temporal sequence is inconsistent with the onset of the event and the study intervention and/or a causal relationship is considered biologically implausible).

### **8.3 Expected AEs**

Expected adverse events (AEs) will be captured through interviews at 12, 24 and 36 weeks, based on the Health Status Update questionnaire. The following are expected adverse events that have been listed in the informed consent form:

- Muscle soreness
- Fatigue
- Chest pain
- Breathing problems
- Cardiac event
- Fall (with or without injury)

### **8.4 Reportable AEs (RAEs)**

Reportable AEs are events that have potential implications for participant safety and that require individual reporting. RAEs will be defined as events that fall into at least one of the following categories:

1. Serious adverse event (SAEs) - SAEs will be defined as any adverse event that results in death, is life threatening, or places the participant at immediate risk of death from the event as it occurred, requires or prolongs hospitalization, causes persistent or significant disability or incapacity, results in congenital abnormalities or birth defects, or is another condition which investigators judge to represent

significant hazards. Only SAEs that are possibly related to the study will be reported.

2. Unexpected AEs - An unexpected AE is defined as medical events that occur during study participation, but do not commonly occur in the study population and which are not listed in the informed consent document or study protocol.
3. AEs related or possibly related to the research intervention – defined as any AE which in the opinion of the principal investigator, the incident, experience or outcome more likely than not was caused by the procedures involved in the research.

Events that cannot be clearly defined as “reportable” will be discussed with the study physician and the PI to determine if they should be reported. All reportable events will be captured on an Adverse Event form which will be filed in the participant binder and then reported using the following guidelines.

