### Summary of Modifications to Protocol Version 1.3 for Version 1.4

| Version
(date)          | Section | Brief Summary of Modification                                                                                                                    |
|----------------------------|---------|--------------------------------------------------------------------------------------------------------------------------------------------------|
| Version 1.4
(8/19/2016) | 8.5-8.7 | Updated information on who RAEs should be reported to and in which order. SAEs that are not related to the protocol will not be considered RAEs. |
|                            |         |                                                                                                                                                  |
|                            |         |                                                                                                                                                  |
|                            |         |                                                                                                                                                  |
|                            |         |                                                                                                                                                  |
|                            |         |                                                                                                                                                  |
|                            |         |                                                                                                                                                  |

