## **8.5 Reporting of Events**

The study PI has primary responsibility for the safety of participants as it relates to the study protocol. The study coordinator will be responsible for reviewing adverse events and assuring accurate and timely reporting of the adverse events. The co-investigators (including study physician) will review, evaluate and classify adverse events and provide follow-up for events until they are resolved. The DSMB will be responsible for monitoring study data for evidence of adverse effects attributable to participation in the study. The PI will be responsible for reporting study-defined AEs and SAEs to the University of Pittsburgh institutional review board (IRB) according to their timeline and format. The reporting sequence of RAEs will be as follows: trial coordinator, principal investigator, [name] (Study MD), IRB, [name] (DSMB) and [name] (NIA). [name] and [name] will determine which RAEs will be shared with the entire DSMB.

**8.5.1 Serious Adverse Events.** The occurrence of SAEs will be obtained on an Adverse Event form during the 12, 24 and 36 week testing sessions and by any study staff member who learns of a serious event. All study staff will be trained to recognize when there is a SAE and to follow appropriate reporting procedures as they become aware of a reportable event.

SAEs possibly related to the study will be reported to the University of Pittsburgh IRB, the DSMB, and NIA within 24 hours of learning of the event. The expedited report of the SAE will be submitted by telephone, fax, or email. Recognizing that the information available during this 24 hour period may not be sufficient to permit accurate completion of the required adverse event reporting forms, a detailed written SAE report will be completed as soon as the information is available. Follow up information can be requested by the DSMB or the NIA or its representative.

**8.5.2 Unexpected Adverse Event.** An unexpected AE may be witnessed by a member of the research team or a staff member may be told about the occurrence or an

unexpected event that may meet the criteria for reporting. Unexpected AEs that have a potential relationship to study procedures and activities will be reported to the University of Pittsburgh IRB and the DSMB within 24 hours of learning of the event.

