#### 8.8 Reporting Expected AEs and RAEs to the DSMB

The DSMB will review tabulated data on non-serious and expected AEs on a semi-annual basis and monitor for adverse event rates out of proportion to those expected. The PI will forward the individual Reportable Adverse Event Records, including a narrative for each event, as well as a table showing all RAEs to the DSMB and NIA semi-annually. The DSMB will review all RAEs that are temporally related to the interventions in aggregate form at its scheduled meetings.

All RAEs that relate to hazards of the study interventions or are cause for urgent concern will be reported to the DSMB chairperson, the NIA and the University of Pittsburgh IRB immediately after recognition of their importance. If the DSMB chairperson concludes that an RAE is of universal and immediate concern, the DSMB chairperson may recommend convening the DSMB to review participant safety based on any individual report or accumulating evidence, including evidence according to treatment assignments.

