### **10.4 Interim Analysis**

We do not plan to perform any interim analyses for efficacy. We will follow the recommendations of the external Data and Safety Monitoring Board (DSMB) to establish the specific rules for interim analyses for safety, either before commencement or very early stages of the trial. Specifically, we a priori plan to use the proportion of completed person-time of follow-up as the information statistic; test-statistic for comparison of proportions of (serious) adverse events to define the Brownian motion process; and an alpha-spending function discussed in Lan and DeMets (1983) to define a safety boundary. We will defer to the recommendation of DSMB regarding specific time points for interim safety analyses (expecting them to be approximately annually or otherwise coincide with DSMB meetings); whether the functional form of the alpha-spending function should be Pocock, O'Brien-Fleming or another function; and any other aspect of interim safety monitoring.

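### Protocol version 1.4 contradicts itself on whether an unrelated SAE is a reportable event, leaves some of these SAEs without an assured route to the safety monitor or the DSMB, and does not define which SAEs feed the safety boundary

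*Supplement*

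**What the plan says.** All of the following stand in the current protocol, version 1.4.

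- **Section 8.2** makes an RAE of "any event that meets the criteria for an SAE, is unexpected, or results in injury to the participant" under study supervision. For SAEs there is no relatedness condition. **Section 8.2.1** gives an example in the same sense: "mild chest pain may results in a day's hospitalization and thus would be classified as a RAE".
- **Section 8.4**, category 1, adds to the SAE definition: "Only SAEs that are possibly related to the study will be reported". **Section 8.5.1** agrees: "SAEs possibly related to the study will be reported to the University of Pittsburgh IRB, the DSMB, and NIA within 24 hours". The summary of modifications for version 1.4 gives the intent: "SAEs that are not related to the protocol will not be considered RAEs".
- **Section 8.1** does not name SAEs among the reportable events.
- **Section 8.2.3** says that the principal investigator, with the co-investigators and an independent safety monitor, "will determine the degree to which RAEs are related to study procedures using the criteria below". **Section 8.6** forwards RAEs to that monitor.
- **Section 8.8** describes the DSMB's regular material. One part reads: "The DSMB will review tabulated data on non-serious and expected AEs on a semi-annual basis". The other is the individual RAE records with a table of all RAEs, also semi-annual.
- **Section 10.4** plans a safety boundary that uses a "test-statistic for comparison of proportions of (serious) adverse events to define the Brownian motion process". It mentions neither relatedness nor a data source.

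**The concern.** Staff who meet an unrelated hospitalisation cannot tell from section 8 whether it is an RAE, and that classification decides whether the safety monitor sees it and whether it enters the RAE table.

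The order of steps is also awkward. Relatedness is to be judged, with the monitor, for RAEs. Under 8.4, however, an SAE becomes an RAE through category 1 only once someone has called it possibly related. An SAE set aside at that first step can miss the independent judgement.

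The statistical stake is that a randomised comparison of all SAEs by arm needs no causality judgement, whereas a comparison of attributed SAEs depends on one. A DSMB that sees only attributed SAEs could miss an excess made up of events that were each, one at a time, called unrelated.

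**Working it through.** The plan gives no figure on this point to reproduce, so the main check is textual.

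**Step 1: the definitions.** An SAE judged unrelated is an RAE by 8.2 and 8.2.1. Category 1 of 8.4, 8.5.1 and the stated intent of the amendment say that it is not. These cannot all hold.

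**Step 2: trace one event.** Take a hospitalisation for a common illness that is not on the 8.3 list and is judged unrelated.

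| Route | Does it apply? |
|---|---|
| 8.4 category 1 (SAE) | No, not possibly related |
| 8.4 category 2 (unexpected) | No; the event must be uncommon in the population and also unlisted |
| 8.4 category 3 (related or possibly related) | No |
| 8.8 table of all RAEs | No, if 8.4 governs; yes, if 8.2 governs |
| 8.8 tabulation of non-serious and expected AEs | No, if both conditions are needed; if the phrase means non-serious events plus expected events, only if the event counts as expected |
| 8.1, expected AEs sent through the database | Not by the 8.3 list; perhaps by 8.2.2, which also treats events attributable to the participant's condition or population as expected |
| 8.6 safety monitor | No, if 8.4 governs |

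Every route to the DSMB or the monitor rests on choosing one of two competing readings. Section 8.2.2 does not settle the matter, because it repeats the attribution wording under both expected and unexpected.

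**Step 3: the threshold.** In 8.2.3 an event is possibly related even if other factors could readily have produced it. Category 3 of 8.4 puts related and possibly related together but requires that the research more likely than not caused the event. The filter therefore has two different thresholds.

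**Step 4: the boundary, illustration only.** The documents give no SAE rate. The nearest figure, in 7.1.2, is under 1% for major risks such as a cardiac event or a fall, which is at most 124 × 0.01 = 1.24 events per arm. It does not cover all hospitalisations. The rates below are assumptions. The 124 per arm is from 10.5.1.

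Pooled two-proportion statistic: z = (p2 − p1) / √[p̄(1 − p̄)(2/124)].

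- All SAEs, 10 v 20: p1 = 0.0806, p2 = 0.1613, p̄ = 0.1210, standard error 0.0414, z = 0.0806/0.0414 = 1.95.
- One in five kept in each arm, 2 v 4: p1 = 0.0161, p2 = 0.0323, p̄ = 0.0242, standard error 0.0195, z = 0.0161/0.0195 = 0.83.

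Power for a single look, two-sided 0.05, 124 per arm, is Φ[(p2 − p1 − 1.96·SE0)/SE1], with SE0 pooled and SE1 unpooled:

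| Assumed SAE rates | All SAEs | 50% kept | 25% kept | 10% kept |
|---|---|---|---|---|
| 5% v 10% | 0.32 | 0.18 | 0.11 | 0.07 |
| 5% v 15% | 0.75 | 0.44 | 0.24 | 0.12 |
| 10% v 20% | 0.60 | 0.32 | 0.18 | 0.10 |
| 10% v 25% | 0.88 | 0.55 | 0.30 | 0.14 |

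The fraction kept is taken as equal in both arms.

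**The case against.** A reader might infer that every unrelated SAE vanishes from the DSMB's view. The documents do not support that. The 8.4 categories are alternatives, and category 2 has no relatedness condition, so an unrelated but unexpected SAE is still an RAE and enters the RAE table; 8.5.2 limits only its 24-hour report. Section 8.1 sends expected AEs to the DSMB through the database without excluding serious ones, and the 8.3 list includes cardiac events and falls. Under 8.2.2 an expected event that exceeds its anticipated frequency or severity becomes unexpected and reportable. The 8.2.3 definition of possibly related is broad enough that a cardiac event soon after a session could well qualify.

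A reader might also infer that attribution is made by people who know the arm. Section 5.2 says only that participants and treating therapists cannot be blinded. It is silent on the investigators who classify events, and the follow-up assessors, at whose sessions SAEs are collected, are blinded.

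Nor is the classification wholly circular, since 8.5 has the co-investigators, including the study physician, classify adverse events generally. Section 10.4 has no relatedness filter, SAEs are still captured at 12, 24 and 36 weeks, and further details are left to the DSMB. In the illustration even the unfiltered z of 1.95 falls short of 1.96, so it shows no lost stopping signal.

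These points stand, and they narrow the concern. They do not remove the conflict between 8.2 and 8.4, the gap for unrelated SAEs that are not unexpected, the possible bypass of the safety monitor, or the undefined input to 10.4. Restricting expedited reporting was a deliberate choice and is not the fault here.

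**Conclusion.** The point holds in three parts. First, the contradiction between 8.2 with 8.2.1 and 8.4 with 8.5.1 is on the face of the current text and needs no assumption. Second, an SAE that is unrelated and not unexpected has no assured route to the safety monitor or to a DSMB table; for events on the expected list, 8.1 and the wider reading of 8.8 may close the gap to the DSMB but not to the monitor. Third, 10.4 does not say which SAEs it counts.

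It would go too far to conclude that the boundary loses events. That would follow only if it were fed from the reported SAEs, which no section says. The size of that loss is known only under assumed rates: for 10% v 20%, power falls from 0.60 to 0.18 if a quarter of SAEs are kept. The efficacy analysis is not affected. Severity: should-fix.

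**What to change.** 1. Reconcile 8.1, 8.2, 8.2.1, 8.4 and 8.8 to a single RAE definition, and have 8.8 say whether its first tabulation covers events meeting both conditions or either one.
2. Leave the expedited reporting rule for possibly related SAEs as it is.
3. Include all SAEs, whatever the attribution, by arm in the semi-annual DSMB tables, with the attribution visible to the safety monitor.
4. State in 10.4 that the boundary statistic uses all-cause SAEs.

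The cost is a short amendment, one more table from data already captured on the Adverse Event form, and a few more events for the existing monitor to see.
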